### Ethical Considerations

The study protocol has been approved by the local Ethics Committee of the Medical Faculty and the University Hospital Tuebingen (reference 444/2023BO2) and has been registered at ClinicalTrials.gov with the number NCT06680336. The study will follow the ethical principles for medical research involving human participants of the Declaration of Helsinki, adopted by the 18th General Assembly of the World Medical Association (World Medical Association, 1964). All patients or their legal guardians will provide informed consent before study enrollment.

This study protocol comes with important ethical considerations, given the vulnerability of patients with acute stroke, particularly those with PSD. Ethical responsibility and patient safety are central. To minimize the burden, neuropsychological testing and MRI sessions are kept as short as feasible and can be paused or rescheduled depending on the patient’s condition. Testing is stopped immediately if signs of distress or fatigue are observed. Clinical staff remain available throughout all procedures. We believe that including patients with cognitive vulnerability is ethically justified, as they are often underrepresented in research. However, their inclusion is balanced with stringent safeguards to ensure that participation does not place undue burden on their health or recovery. The data collected during the study will be pseudonymized to ensure the confidentiality of participants. All personal information will be treated with the utmost care and in accordance with applicable privacy regulations, including data protection laws. Patients are provided with a monetary compensation for their time and effort in accordance with the ethical guidelines of the study.

### Neuropsychological Assessment and Clinical Scores

We followed a multicomponent cognitive assessment strategy using standardized tests, questionnaires, and clinical scores in order to ensure a comprehensive assessment of PSCI. The selection of tests and domains aligns with the recommendations of major stroke organizations, such as the European Stroke Organisation and the Canadian Stroke Network [39,40]. The following domains were defined: attention and information speed, executive functions, verbal memory, language, visuospatial construction, and orientation (Table 1). In general, the tests, questionnaires, and clinical scores used in this study protocol are appropriate for our elderly study population, with available normative data. The order of test administration is standardized to ensure consistency across participants and is arranged to alternate between cognitive domains and varies in modality (eg, verbal vs visuospatial) to reduce cognitive load and prevent fatigue. To reduce practice effects across sessions, we use official parallel test forms when available. In consideration of the elderly study population, the selection of tests and questionnaires was also based on font size, or in cases where applicable, the font size was increased. Table 1 illustrates the questionnaires and clinical scores, as well as their targeted components used in this study. The neurological examination comprises the standardized NIHSS [35]. Some parts of the assessment will be digitalized using a tablet app called TuCAN (Tübingen Cognitive Assessment for Neuropsychiatric Disorders) [41] and a digitizer pencil. The TUCAN app was designed for elderly individuals and has previously been evaluated in healthy older populations [42,43]. Furthermore, it has been used to assess cognitive functions in 2 clinical populations: patients with cognitive impairment and patients with stroke [44,45]. To address potential unfamiliarity with digital technology in older patients with stroke, patients complete a short familiarization task before the formal assessment begins, during which they are asked to write a sentence or a few words on the tablet.

**Table 1. T1:** Standardized tests, questionnaires, and clinical scores with the corresponding targeted domain.

Target domain and test/clinical score/questionnaire	S1^a^	S2	S3
Attention and processing speed			
TMT^b^—Part A [46]	✓	✓	✓
NAB^c^ Module Attention [47]	✓	✓	✓
Executive functions			
WM^d^ span within NAB Module Attention [47]	✓	✓	✓
TMT—Part B [46]	✓	✓	✓
Verbal memory			
MIS^e^ within MoCA^f^ [48]	✓	✓	✓
Language			
LIS^g^ within MoCA [48,49]	✓	✓	✓
Visuospatial construction			
VIS^h^ within MoCA [48,49]	✓	✓	✓
Orientation			
OIS^i^ within MoCA [48,49]	✓	✓	✓
Cognitive impairment			
MoCA [48]	✓	✓	✓
Questionnaires assessing cognitive functioning			
Self-rating CFQ^j^ [50]	✓		
Relative questionnaire: IQCODE^k^ [51]	✓		
Depression			
GDS^l^ [52]	✓	✓	✓
Quality of life			
SF^m^-12 [53]	✓		✓
Global disability			
(p)mRS^n^ [54]	✓		✓
Delirium screening			
ICDSC^o^ [55]	✓	✓	✓
Stroke symptoms			
NIHSS^p^ [35]	✓	✓	✓
Other variables			
Verbal intelligence test (MWT-B^q^ [56])	✓		
Demographics	✓		
Stroke location, medical interventions, comorbidities, etc	✓		

a S: session.

b TMT: trail making test.

c NAB: Neuropsychological Assessment Battery.

d WM: working memory.

e MIS: memory index scale.

f MoCA: Montreal Cognitive Assessment.

g LIS: language index scale.

h VIS: visuospatial index scale.

i OIS: orientation index scale.

j CFQ: cognitive failure questionnaire.

k IQCODE: Informant Questionnaire on Cognitive Decline in the Elderly.

l GDS: Geriatric Depression Scale.

m SF: Short Form health survey.

n (p)mRS: (pre)modified Rankin scale.

o ICDSC: Intensive Care Delirium Screening Checklist.

p NIHSS: National Institutes of Health Stroke Scale.

q MWT-B: German intelligence test *Mehrfach-Wortschatz-Intelligenztest*.

### Neuroimaging Protocol

Functional and structural MRI data will be acquired using a 3 Tesla Siemens Prisma whole-body imaging system (Siemens), equipped with a 64-channel head coil. Functional and diffusion-weighted images are acquired using the Minnesota CMRR multiband accelerated pulse echo planar imaging (EPI) sequences [57]. For functional imaging, a T2*-weighted EPI sequence with repetition time (TR) of 800 ms, echo time (TE) of 37 ms, flip angle of 52°, 72 axial slices, 2-mm slice thickness, field of view (FoV) of 208 mm (whole-brain coverage was ensured by tilting the FoV to the individual anterior commissure – posterior commissure line) was used. Diffusion tensor imaging data are acquired using an EPI sequence with the following parameters: TR of 2100 ms, TE of 62 ms, flip angle of 72°, 92 slices, 1.50-mm isotropic resolution slice thickness, FoV of 210 mm, and 64 diffusion directions at *b* value of 1500 s/mm^2^. For anatomical images, a T1-weighted magnetization-prepared rapid gradient-echo sequence with the following parameters: TR of 2500 ms, TE of 2.22 ms, 208 axial slices, 0.8-mm slice thickness, FoV of 256 mm will be used. Furthermore, to assess the stroke area, a standard Siemens Prisma T2-weighted fluid-attenuated inversion recovery sequence with TR of 9000 ms, TE of 81 ms, 36 axial slices, 4-mm slice thickness, and FoV of 230 mm will be used.

### Working Memory Task

The working memory task will be a modified version of a well-known Sternberg task [58-62] with 4 task conditions. Given that our study population comprises older patients with stroke with PSD and without PSD, further modifications of a previously published Sternberg task [58,59,61,62] were necessary. Previous studies have reported difficulties regarding the feasibility of performing a working memory task after delirium [28,32], which we have taken into consideration. To enhance feasibility, the following modifications were implemented: [1] reduction of task difficulty by reducing the number of stimuli in the memory set from 5 to 4 items [2], shortening of the total task duration [3], adjustment of experimental conditions by including objects to enable the examination of the visual-spatial components of working memory.

This modified version of the Sternberg task consists of 4 task conditions with different working memory categories, that is, verbal and visual items. In detail, 2 conditions comprise letters (letter condition [LE] and letter control condition [LC]) and 2 comprise objects (object condition and object control condition), as illustrated in Figure 2. The letters in the letter condition (LE) consist of consonants, and the letters in the control condition (LC) consist of vowels. In order to map the differences in letters (eg, FGMP, as in the letter conditions) onto the differences in objects, several semantic categories were selected for the object conditions, for example, pictures of daily life items, clothes items, kitchen tools, and electrical devices. All objects were derived from the bank of standardized stimuli line drawings [63,64]. To minimize condition-dependent effects such as differences in visual activations, eye movement, or spatial attention, all stimuli are presented on a white screen, at a fixed position and in black font or black line drawings (Figure 2). All conditions are presented 5 times in a pseudo-randomized and counterbalanced order. The experiment will be performed using the Presentation software (version 23.0; Neurobehavioral Systems, Inc) [65].

**Figure 2. F2:**
[figure not shown]
Modified version of the Sternberg task (working memory task) with 4 task conditions (letters, letter control, objects, and object control) each consisting of an encoding and a retrieval phase.

Each trial consists of an encoding phase and a retrieval phase. During the encoding phase, a set of 4 letters or objects (memory set) is presented and has to be memorized. After a variable interstimulus interval (1000‐1600 ms, randomly jittered in steps of 200 ms), 4 single-letter probes (2 targets, 2 nontargets) are presented for 1800 ms each in the retrieval phase (each followed by a fixation cross for 1200 ms), and the patient has to indicate after each single-letter probe whether the probe was part of the previously shown memory set or not. Patients have to press the left button on an MRI-compatible response pad to indicate that the single-letter probe was part of the memory set or press the right button if it was not. The total duration time of the working memory task is approximately 6.45 minutes. Figure 2 illustrates the conditions and trials of the working memory task.

### Statistical Analysis

#### Multicomponent Neuropsychological Assessment

In general, analysis will be conducted using SPSS Statistics (version 28.0.0.0; IBM Corp) [66] and MATLAB (R2024a; MathWorks Inc) [67].

In a first step, the analysis of the abovementioned tests, questionnaires, and clinical scores will be conducted according to the applicable manual. Raw scores will be transformed into norm-referenced *z* scores if standardizations are available.

In the second step, for the assessment of PSCI, a global and a domain-specific PSCI score will be defined in accordance with the guidelines of the International Society for Vascular Behavioral and Cognitive Disorders [68] and similarly to previous studies [39,69-72]. Further, the distinction between average cognitive functioning and mild, moderate, or severe cognitive impairment will be made according to the performance level on norm-referenced *z* scores, which is in line with the recommendations of multiple neuropsychological societies [73]. In detail, PSCI is a 5-level performance score. Performance level within 1 SD below or above the mean is defined as average cognitive functioning (PSCI=0). A range between 1 and 2 SDs below the mean (between third and 16th percentile) on at least 1 cognitive domain is defined as mild cognitive impairment (PSCI=1). A performance level 2 SDs below the mean (lower than the third percentile) in at least 2 domains is defined as moderate (PSCI=2), while a performance level 3 SDs below the mean (lower than the first percentile) in at least 2 cognitive domains or 2 SDs below the mean in most of the domains is defined as severe cognitive impairment (PSCI=3). Due to increased mortality in the PSD group, and to accommodate clinical realities as well as access feasibility of our study protocol, we use an intention-to-treat analysis for the primary end point. Therefore, we have added a level (PSCI=4), which reflects the death of a patient before the 3-month follow-up session. The following domains are defined: attention and information speed, executive functions, verbal memory, language, visuospatial construction, and orientation (Table 1). If a cognitive domain is represented by more than 1 test, the mean of the *z* scores will be used. We do not apply explicit weighting to individual test components when creating the composite scores for global and domain-specific poststroke cognitive function to ensure that each test within a domain contributes equally to the composite score, maintaining consistency with established neuropsychological standards. The primary endpoint will be a between-group comparison of the cognitive outcome, defined as global PSCI at a 3-month follow-up (S3). The groups will also be balanced for age and sex. Secondary outcome measures will be a between-group comparison of the domain-specific PSCI at a 3-month follow-up (S3).

Further, multivariate linear regression models will be used to analyze multi-item prognostic or predictive tools for cognitive outcome (eg, global PSCI) at the follow-up measurement (S3) by multimodal parameters assessed during the acute phase poststroke (S1), such as NIHSS, acute treatment, and working memory performance during fMRI or fMRI connectivity measures. As some tests will be digitalized using a tablet and a digitizer pencil, new parameters representing search behavior, for example, time on surface and time in air [42,74], will be recorded and might help to differentiate between PSD and non-PSD groups or identify patients with stroke with a high delirium risk.

Missing data will be handled in the following manner. For missing data in a 2-test subdomain, we plan to use the *z* score of the other test within the same subdomain. For missing data in a single test subdomain, we plan to use a multiple imputation approach or maximum likelihood estimation.

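### The level rule behind the primary endpoint leaves out one pattern (a single domain below -2 SD, no other below -1 SD), and its severe cut-off carries a percentile that does not match

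*Protocol article*

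**What the plan says.** The rule is in the Protocol article, Methods, Statistical Analysis, Multicomponent Neuropsychological Assessment. It is introduced as a full definition: "In detail, PSCI is a 5-level performance score". The levels are:

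- **0, average:** "Performance level within 1 SD below or above the mean is defined as average cognitive functioning (PSCI=0".
- **1, mild:** "A range between 1 and 2 SDs below the mean (between third and 16th percentile) on at least 1 cognitive domain".
- **2, moderate:** "A performance level 2 SDs below the mean (lower than the third percentile) in at least 2 domains is defined as moderate (PSCI=2".
- **3, severe, first arm:** "a performance level 3 SDs below the mean (lower than the first percentile) in at least 2 cognitive domains".
- **3, severe, second arm:** "or 2 SDs below the mean in most of the domains is defined as severe cognitive impairment (PSCI=3".
- **4, death:** "we have added a level (PSCI=4), which reflects the death of a patient before the 3-month follow-up session".

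Six domains enter: "attention and information speed, executive functions, verbal memory, language, visuospatial construction, and orientation". The same section makes the between-group comparison of global PSCI at three months the primary endpoint and declares an intention-to-treat analysis for it. It does not say that the highest matching level applies, and it gives no number for the majority of domains in the second severe arm.

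**The concern.** An ordinal primary endpoint must give every patient exactly one level. Two features of this rule stand in the way.

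**A missing pattern.** Mild is bounded on both sides, at -1 and -2 SD. Moderate and severe both need at least two affected domains. One isolated domain beyond -2 SD, with nothing else below -1 SD, falls between them. It is not average either, because that domain is not within 1 SD of the mean. The ordering is also odd: the patient becomes classifiable, as mild, only when a further deficit is added.

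**A mismatched cut-off.** Under a normal distribution, -3 SD and the first percentile are different points, yet the first severe arm gives them as one criterion.

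The groups are planned at 20 each, so a few reassigned patients can shift an ordinal comparison. Dropping an unclassified patient would conflict with the declared intention-to-treat analysis. Choosing a level or cut-off once scores and group membership are known would be a post hoc decision about the primary endpoint.

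**Working it through.** **Step 1. The plan's own SD and percentile pairs, checked against the standard normal distribution.**

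| Cut-off in SD | Percentile in the article | Phi(cut-off) | z at the article's percentile |
|---|---|---|---|
| -1 | 16th | 15.87% | -0.99 |
| -2 | third | 2.28% | -1.88 |
| -3 | first | 0.135% | -2.33 |

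The first pair agrees, the second agrees loosely, and the third does not. In the norm population 0.01 / 0.00135 = 7.4 times as many people lie below the first percentile as below -3 SD. Of those below the first percentile, 1 - 0.135 = 86.5% are not below -3 SD.

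**Step 2. Is the rule exhaustive?** Put each of the six domains into one of four bands: A (above -1 SD), B (-1 to -2), C (-2 to -3), D (below -3). There are C(9,6) = 84 unordered patterns. The literal conditions are:

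- level 0: all six in A
- level 1: at least one in B
- level 2: at least two in C or D
- level 3: at least two in D, or a majority in C or D (taken as at least 4 of 6, an assumption)

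Exactly 2 of the 84 patterns meet no level: one C with five A, and one D with five A. A further 61 meet more than one level, with no precedence stated; taking the highest is the obvious reading. The patterns are not equally likely, so these counts show where the rule fails, not how often.

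Examples:

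- one domain at -2.5, five average: no level
- one domain at -2.5, one at -1.5, four average: level 1
- two domains at -2.6, four average: level 2 by the SD text, level 3 by the percentile

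**Step 3. How often?** The article gives no distribution of domain scores, so these are simulations on assumed values: 400,000 patients per setting and six equicorrelated normal z scores with unit variance.

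| Assumed pattern | Mean | Correlation | Fit no level |
|---|---|---|---|
| Diffuse | 0 to -1.5 | 0.3 to 0.7 | 0.2% to 2.9% |
| One domain an extra -1.5 SD lower | -0.5 | 0.3 to 0.5 | 8.5% to 8.9% |
| One domain an extra -1.5 SD lower | -1 | 0.3 to 0.5 | 4.6% to 5.4% |

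For 40 patients, 2.9% is 0.029 x 40 = 1.2 patients, and 5-9% is 2 to 3.6 patients. Deaths go to level 4, so these are upper figures.

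**Step 4. Size of the cut-off mismatch.** In the same diffuse settings, 26% to 49% of patients rated moderate by the SD text become severe if the percentile is used. That is 0.5% to 16% of all patients. Patients who are severe through the second arm do not move, because that arm uses only -2 SD.

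**The case against.** **One sensible resolution exists.** Since moderate needs two domains, a single impaired domain is naturally mild, and a scorer has no textual basis for calling it average. This is a fair account of the probable intent, and the fix below adopts it. It does not make the written rule complete: mild stops at -2 SD.

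**The z scores govern.** The section says that levels follow norm-referenced z scores, so the percentiles may be only glosses. The gloss is also literally true, since 0.135 is below 1. This largely stands, and it makes the mismatch a drafting fault more than an outright contradiction. The 16th percentile does match -1 SD, however, so a scorer working from percentile norms could take the brackets as equivalents.

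**The unseen plan may settle it.** It may add precedence or a number for the majority of domains. But the article states the level rule in full, so the gap lies in a stated rule and is not a detail left out.

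Several stronger readings that a reader might infer are not supported:

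- *Any patient with one severely impaired domain is unclassified.* A second domain between -1 and -2 SD makes the patient mild. With diffuse deficits (means -0.5 to -1.5, correlation 0.3 to 0.5), only 3% to 15% of patients with exactly one domain below -2 SD fall in the gap.
- *A fifth or more of the trial is lost.* Reaching 20-24% (8 to 10 of 40) requires every patient to carry an extra -2.5 SD in one domain while the other domains average -0.5 SD. The Introduction describes deficits across several domains, and aphasia, one focal source, is an exclusion criterion.
- *Every moderate or severe rating is in doubt.* The second severe arm is an ordinary alternative criterion and does not use the disputed cut-off.
- *A domain above +1 SD is also unclassified.* This is true of the wording, but trivial: the score grades impairment and the intent is plain.

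**Conclusion.** The point holds in a limited form. As written, the primary endpoint's level rule is not exhaustive. The uncovered pattern is exactly one domain more than 2 SDs below the mean with no other domain below -1 SD. This follows from the wording alone and needs no assumption.

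Its frequency does rest on assumptions: about 0.2-3% of patients with diffuse deficits, or roughly 0 to 1 of 40, and about 5-9% if one domain carries an extra -1.5 SD and the other domains average -0.5 to -1 SD. Larger shares need strongly focal deficits, which the article does not describe.

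The percentile attached to the severe cut-off does not match -3 SD. Because the z-score text is probably operative, this matters only if someone scores from percentiles. Some patients would then move from moderate to severe, but none of those already severe through the second arm.

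The study calls itself an underpowered proof of concept, which limits the consequences. The rule still has to give one level per patient before it can serve as the primary endpoint.

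**What to change.** Replace the level paragraph with a rule applied from the top down, on domain z scores only, stopping at the first level met:

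1. **4:** death before the 3-month session.
2. **3:** z <= -3 in at least 2 domains, or z <= -2 in a stated number of domains (for example, at least 4 of 6).
3. **2:** z <= -2 in at least 2 domains.
4. **1:** z <= -1 in at least 1 domain, including a single domain at or below -2.
5. **0:** all remaining patients, including those with domains above +1.

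Delete the percentiles, or correct them to 2.3rd for -2 SD and 0.13th for -3 SD.

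Settle this before the 3-month data are analysed; the Results section places the analysis at the start of 2026. The cost is one paragraph of wording. No new data are needed, and patients already assessed can be rescored from their stored z scores.

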The specific objectives of this study are to (1) compare the global PSCI of patients with and without PSD at a 3-month follow-up, (2) compare domain-specific cognitive outcome measures of patients with and without PSD at a 3-month follow-up, (3) generate preliminary data regarding the differentiation between PSD-related and stroke-related cognitive impairment using behavioral and fMRI connectivity measures, and (4) contribute toward developing protective and prognostic tools for the early detection and treatment of PSD.

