**Figure 1. F1:**
[figure not shown]
Overview of the RECOVER (Cognitive Recovery After Poststroke Delirium) study procedures. DSM-5: *Diagnostic and Statistical Manual of Mental Disorders, Fifth Edition*; DTI: diffusion tensor imaging sequence; FLAIR: fluid-attenuated inversion recovery sequence; ICDSC: Intensive Care Delirium Screening Checklist; MPRAGE: T1-weighted magnetization prepared rapid acquisition with gradient echoes sequence; MRI: magnetic resonance imaging; NIHSS: National Institutes of Health Stroke Scale; S1: session 1; S2: session 2; S3: session 3; T2*: T2-weighted echo planar imaging sequence; WM: working memory.

The three measurement points are as follows:

S1 during the acute phase poststroke (≤48 h after hospital admission; ≤96 h after stroke onset and before PSD development)S2 during the postacute phase poststroke (5‐14 d poststroke, depending on delirium recovery)S3 follow-up at 3 months poststroke (approximately 90 d poststroke)

Patients with stroke will be admitted to the Stroke Unit where a screening visit will be conducted, including a review of the inclusion and exclusion criteria. Following the review, written informed consent will be obtained from the patient or, if applicable, the legal guardian. Once consent has been obtained, the patient will be enrolled in the RECOVER study.

Each measurement (S1-S3) consists of a clinical examination, a multicomponent neuropsychological testing, and an MRI protocol. The MRI protocol is designed to acquire both structural (anatomical) data, as well as functional data (see the *Neuroimaging Protocol* section for more details). The clinical examination includes the National Institutes of Health Stroke Scale (NIHSS) [35] and will take approximately 15 minutes. The multicomponent neuropsychological assessment and the MRI scan (including positioning of patient) will each require 45‐60 minutes. A more detailed description is provided in the *Neuropsychological Assessment and Clinical Scores* section. S1 and S2 will be conducted as in-patient measurements, and the S3 3-month follow-up measurement will be conducted as an out-patient measurement.

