### Study Population and Recruitment

This longitudinal proof-of-concept study aims to include a total of 40 patients with acute stroke, equally distributed in a PSD (n=20) and a non-PSD group (n=20). All the patients with acute stroke will be recruited from the wards of the Neurological Department of the University Hospital Tübingen.

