While this was beyond the scope of this proof-of-concept study, future studies should be initiated as multicenter trials to enhance the generalizability and robustness of the findings. Increasing the sample size will be essential to achieve adequate group sizes and improve statistical power. Additionally, balancing groups according to key variables, such as lesion location or stroke severity, would strengthen the validity of comparisons.

Another important aspect is the consideration of the amount of cognitive rehabilitation on PSCI. Unfortunately, this was beyond the scope of this study, and this protocol includes only documentation of whether rehabilitation was received and its duration. A detailed evaluation of the effect of cognitive rehabilitation impact on long-term outcomes should be addressed in future studies. Another consideration would be extended follow-ups, for example, after 6 and 12 months, to better capture cognitive trajectories.

This protocol represents a proof-of-concept study designed to systematically and comprehensively examine cognitive functions in critically ill patients with acute stroke with and without delirium. It combines comprehensive neuropsychological testing with a multimodal MRI protocol, including digitalized assessments and task-based functional MRI. By addressing a significant clinical gap and using innovative methodologies, this study lays essential groundwork toward larger, adequately powered studies.

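### The primary three-month comparison of PSD and non-PSD patients names no control for pre-delirium cognition or stroke severity, both measured at S1, so it is weak evidence for separating PSD-related from stroke-related impairment

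*Protocol article*

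**What the plan says.** All references are to the Protocol article.

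- **Primary comparison** (Statistical Analysis, Multicomponent Neuropsychological Assessment): "The primary endpoint will be a between-group comparison of the cognitive outcome, defined as global PSCI at a 3-month follow-up (S3"). Global PSCI has five levels, 0 to 4, with death before follow-up as level 4. The same paragraph adds "The groups will also be balanced for age and sex".
- **Groups** (Study Population and Recruitment): 40 patients, "equally distributed in a PSD (n=20) and a non-PSD group (n=20"). Under Study Design and General Procedures, the cohort is split after enrolment and before S2, according to whether delirium occurred.
- **Baseline** (Study Design and General Procedures): "S1 during the acute phase poststroke (≤48 h after hospital admission; ≤96 h after stroke onset and before PSD development"). "Each measurement (S1-S3) consists of a clinical examination, a multicomponent neuropsychological testing, and an MRI protocol". "The clinical examination includes the National Institutes of Health Stroke Scale (NIHSS"). Table 1 ticks the cognitive tests and NIHSS at S1, S2 and S3.
- **Use of S1 data against S3 outcome** (Multicomponent Neuropsychological Assessment): a regression for prognostic tools, with S1 NIHSS, acute treatment and fMRI measures as example predictors. PSD status is not named as a term.
- **Aim** (Introduction, objective 3): "generate preliminary data regarding the differentiation between PSD-related and stroke-related cognitive impairment".
- **Discussion**: days since stroke is the one covariate named, as a remedy for variable assessment timing. For future studies, "balancing groups according to key variables, such as lesion location or stroke severity, would strengthen the validity of comparisons".

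**The concern.** Whatever makes a patient prone to delirium may also worsen cognition at three months. The Introduction supplies the link: delirium risk is reported as higher in total anterior circulation infarcts than in other infarct types, and the networks in that territory serve attention, memory and executive function, which are among the outcome domains. The Introduction also faults earlier work for being unable to disentangle delirium from stroke.

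A study that measures cognition and severity before the exposure occurs is well placed to do better, but the stated primary comparison does not use that advantage. Balance on age and sex does not address stroke severity, infarct type or pre-delirium cognition. It also cannot be guaranteed without selecting or discarding enrolled patients, because group membership is known only afterwards. At stake is the reading of the main result: a worse S3 score in the PSD group could reflect the stroke, the delirium or both, and the larger studies this one is meant to inform would inherit that ambiguity.

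**Working it through.** The article gives no effect size, SD or power figure, so there is nothing of its own to reproduce. What follows is an illustration.

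**From the article:** 20 patients per group; true PSD effect set to zero for the check.

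**Assumed:** S1 cognition is worse in the PSD group by g = 0.3, 0.5 or 0.8 SD; the correlation r between S1 and S3 is 0.5 or 0.7; unit SD; two-sided alpha 0.05.

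**Formulas**

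- Spurious S3 gap = r × g.
- Standard error of an unadjusted difference = sqrt(1/20 + 1/20) = 0.316 SD.
- Chance of a nominally significant result = P(|Z + r·g/0.316| > 1.96).

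The same settings were simulated with a five-level outcome (assumed cut-points, 4000 runs per row). The unadjusted analysis was a Mann-Whitney test. The adjusted analysis was a linear model of the level on group and S1 score.

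| g | r | Spurious gap (SD) | Significant, formula | Significant, simulated unadjusted | Significant, simulated S1-adjusted |
|---|---|---|---|---|---|
| 0.3 | 0.5 | 0.15 | 7.6% | 6.5% | 4.8% |
| 0.3 | 0.7 | 0.21 | 10.2% | 8.7% | 4.9% |
| 0.5 | 0.5 | 0.25 | 12.4% | 10.8% | 5.7% |
| 0.5 | 0.7 | 0.35 | 19.8% | 16.5% | 5.2% |
| 0.8 | 0.5 | 0.40 | 24.4% | 20.6% | 5.4% |
| 0.8 | 0.7 | 0.56 | 42.5% | 35.8% | 5.7% |

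With no S1 gap, the simulated rates lie between 4.7% and 5.8% for both analyses.

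**Limits of the check.** In the simulation the S1 score carries all the confounding, so the last column is a best case for adjustment. Death was not modelled separately from the other levels. The gap and the correlation are not in the article.

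**The case against.** The strongest reply is that the article names no test or model for the primary comparison, never says it is unadjusted, and may leave its covariates to an analysis plan that is not shown. Deferring *balance* on severity and lesion location also does not rule out *adjusting* for them. This is fair, and an unseen plan may already contain the adjustment. But the article is not merely silent: it chooses age and sex as the balancing factors, names days since stroke as its covariate, gives S1 NIHSS a role only in the prognostic regression, and leaves balance on severity to later studies.

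Eligibility also helps. Dementia, other neuropsychiatric disorders and aphasia are excluded and NIHSS is capped at 15. This narrows the confounding. Severity can still vary from 0 to 15, and the listed criteria do not restrict lesion location.

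The authors call the study underpowered and its data preliminary, and the Discussion says only that the design may allow the differentiation. That tempers the claim, but small size explains imprecision, not avoidable bias.

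Four stronger readings are tempting and are not supported:

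- *Objective 1 cannot be answered.* It asks for a comparison of patients with and without PSD, and the S3 contrast describes that.
- *The PSD group is known to start with worse strokes or lower reserve.* The article gives no such figure for this restricted cohort, and pre-existing dementia is excluded.
- *The plan ignores S1 data.* This is true only of the stated primary comparison.
- *Adjustment would make 40 patients worth about 62.* With r = 0.6, linear covariance analysis gives an SE of 0.316 × sqrt(1 − 0.36) = 0.253 SD and 40/0.64 = 62.5 patients, but only with no S1 gap. A 0.5 SD gap inflates the variance by 1 + 0.5²/4 = 1.0625, giving 0.253 × sqrt(1.0625) = 0.261 SD and 62.5/1.0625, about 59 patients. Neither figure carries over to the log odds ratio of an ordinal model, so the case for adjustment rests on bias, not precision.

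**Conclusion.** The point holds in limited form. As stated, the primary comparison supports a descriptive association between PSD and S3 cognition (objective 1). It is weak evidence for attributing impairment to PSD rather than to the stroke (objective 3 and the matching claim in the Discussion), because pre-delirium cognition and severity are measured but given no stated role in it.

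The size of the bias cannot be known from the article. Under the assumed range it is 0.15 to 0.56 SD, against a standard error of 0.316 SD, with a nominally significant result in about 7% to 36% of simulated ordinal trials when PSD has no effect. Adjustment would reduce confounding by what S1 captures. It would not by itself separate the two causes, since lesion location and unmeasured factors remain.

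**What to change.** 1. Prespecify the primary analysis as an ordinal regression of S3 global PSCI on PSD status, adjusted for the S1 mean domain z score, S1 NIHSS and age, and for sex if the data allow. Show the unadjusted result alongside.
2. Replace the sentence promising balance with a commitment to report imbalance between the groups in age, sex, stroke severity and lesion location.
3. State that lesion location and unmeasured factors remain uncontrolled, and describe the estimate as an adjusted association. Word objective 3 and the Discussion to match.

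**Cost.** No new data are needed, because cognition, NIHSS, demographics and stroke location are all in Table 1 at S1. The three covariates use about three degrees of freedom. With PSD status and four thresholds the model has 3 + 1 + 4 = 8 parameters for 40 patients, which is why the set must stay small. If prodromal delirium already lowers S1 scores, adjustment may remove part of a real PSD effect, by an unknown amount. This is a further reason to show both results.
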